### Onboarding Procedures

#### Preparing for the Session

Before the participant joins their onboarding Zoom call, the interviewer will review the crisis management protocol, open up the appropriate forms for the participant’s mobile device (iOS or Android), and review the participant tracking sheet to ensure that they have the participant’s information from the screener. The interviewer will join the Zoom virtual conference room 5 to 10 minutes in advance of the participant and will have their camera on for the duration of the call. The participant will not be required to have their camera on. When the participant joins the Zoom call, the interviewer will confirm with the participant that they have 60 to 90 minutes available for the appointment and confirm that the participant is in a safe and private setting.

#### Consenting (All Participants)

The interviewer will open the appropriate consent form for the participant’s phone type (Android or iOS) and study condition (uTECH+YMHP or YMHP only), which is a survey hosted on Qualtrics, and share their screen on Zoom so that the participant can view it simultaneously. The interviewer will remind the participant that they will receive a copy of the document via email at the end of the call. The interviewer will input the participant ID at the top of the page and review study details while regularly asking the participant if they have any questions. The consent form includes a detailed explanation of all study requirements and how their data will be protected. At the end of the consent form, the interviewer will ask if the participant consents to the study. If affirmative, the interviewer will check the box for “I agree to participate in the study,” provide their initials on the survey, and submit the consent survey. If the participant does not consent, then the interviewer will check the box for “I decline to participate in the study,” provide their initials on the document, submit the survey, thank the participant for their time, and end the call. The consent process will take approximately 25 minutes. If the participant consents to participate, then the onboarding session will continue.

#### Installation of the eWellness App (Android Users Only)

Participants who use Android smartphones will receive step-by-step instructions on how to install the eWellness app (version 1.0.24, released January 2023) on their primary smartphone, where it will remain active and collect data for 12 months. The interviewer will send the participant a short link that they can type in their Android internet browser and download the app. The interviewer will guide the participant through the app download and setup process and troubleshoot any technical issues that may arise. If the interviewer or the participant runs into technical difficulties that cannot be resolved at the time of the interview, the interviewer will continue onto the baseline survey and make a note that they will have to complete the app download within a week’s time after consulting with the research team. If the app is compatible with the device and successfully downloads, the interviewer will continue to guide the participant in completing the in-app Wellness Survey. This process will take approximately 15 minutes.

#### Wellness Survey (iOS Users Only)

The Wellness Survey is a Qualtrics survey version of the in-app Wellness Survey that Android users complete. The participant receives a link to this survey through SMS text message, and the interviewer will instruct the participant to complete this short survey. This process will take approximately 5 minutes.

#### PrEP Verification (All Participants)

If the participant endorses current PrEP use, the interviewer will ask the participant to upload a photo of their prescription bottle to the eWellness app, which is routed to a Qualtrics survey that is encrypted with Transport Layer Security for all transmitted data. Participants may also choose to block or cover any personal information they do not wish to share with researchers. This process will take approximately 5 minutes.

#### Social Networking App Download Requests (iOS Users Only)

Participants who use iOS smartphones will receive step-by-step instructions on how to request social networking app downloads from their most frequently used web-based dating apps (such as Grindr or Tinder) and social media accounts (such as Twitter or X, Instagram, Reddit, and Facebook) to send to the research team. The study staff will describe the process specific to each dating app or social media app and either email the instructions to the participant or walk the participant through the process during the Zoom meeting. The participant will then need to download their data and email the files to an encrypted email address managed by the research team. This process will take approximately 10 minutes.

#### Baseline Interview (All Participants)

The interviewer will share their screen to display the baseline survey, which is hosted on the Qualtrics platform, and includes a series of questions about demographics, intimate partner history, sexual health, substance use, intimate partner violence, vaccine hesitancy, effects of COVID-19, and eHealth mobile app tracking and notification preferences. The survey also asks the participants for their preferred payment information. After all questions have been answered, the interviewer will stop sharing their screen and submit the baseline survey. This process will take approximately 30 minutes.

#### YMHP Scheduling (All Participants)

The interviewer will schedule the participant with their first YMHP session through Calendly, a scheduling website, with an interventionist who is not the baseline interviewer. The participant’s first session will be scheduled approximately 1 week after the onboarding and baseline survey (week 1). The interventionist and the participant will receive a calendar invite reminder for this session. Subsequent sessions are scheduled between the interventionist and the participant and will take place in week 2, month 1, and month 2 after onboarding. The scheduling process will take approximately 5 minutes.

#### Closing Out the Onboarding (All Participants)

The interviewer will open the “Locator form” to document the participants’ preferred forms of contact, their phone type, and how they heard about the study. The interviewer will remind the participant of the follow-up surveys at 3, 6, 9, and 12 months; their first YMHP session (if applicable); and when to expect payment (approximately 3-5 business days after each data collection point or YMHP session). This process will take approximately 10 minutes.

#### Postonboarding Activities (All Participants)

Immediately after ending the onboarding session with the participant, the interviewer will download the materials completed by the participant and upload them to a secure, password-protected cloud-based database (such as Box). Afterward, to ensure confidentiality, the interviewer will delete all materials from their computer. The interviewer will also update the participant’s information in a tracking database and send a thank you email to the participant, which will include a copy of the study’s consent form and the University of California, Los Angeles (UCLA) Office of Human Research Protection Program participant bill of rights [62], which details protections for participants within the consent and participation process. This process will take approximately 30 minutes.

#### STI or HIV Testing (All Participants)

Participants will be offered the option of sending STI or HIV test results to the study team at their baseline and 6-month appointment dates. While testing is optional, those who do elect to send results will be compensated US $30 at both points (for a total of US $60) for providing test results for HIV, syphilis, chlamydia, and gonorrhea. Participants will be instructed to send their results in the form of a scanned document, screenshot, or PDF to an encrypted email managed by the study team. All identifying information in the file containing results will be redacted by the research team before being saved in the study’s password-protected, encrypted, cloud-based database. When test results are received, participants will be reminded of their compensation and encouraged to reach out to research staff or their YMHP interventionist if they would like further information or resources.

If requested, participants will be provided HIV, syphilis, gonorrhea, or chlamydia prevention and treatment resources. They will also be asked if they have a health care provider who they could contact for treatment. If they do not, they will be offered a list of sexual health clinics or providers in their area. In addition, participants will be offered a partner notification service to anonymously notify recent sexual partners of a possible STI exposure.

#### YMHP Sessions (All Participants)

##### Overview

YMHP intervention sessions will be held over Zoom, a videoconferencing platform. Session 1 will take place during week 1 (following onboarding), session 2 during week 2, session 3 during month 1, and session 4 during month 2 (Figure 1). All sessions will be audio recorded for intervention fidelity and ongoing intervention training and clinical support. No video or participant names will be captured for the recording. Participants will be asked to change their Zoom name to their participant ID before recording.

**Figure 1 figure1:**
[figure not shown]
uTECH participation overview flowchart. STI: sexually transmitted infection; YMHP: Young Men’s Health Project.

##### Session 1: Engagement, Focusing, and Evoking on the First Target Behavior (Sexual Health or Substance Use)

The interventionist will remind the participant about the YMHP structure and limits of confidentiality. The interventionist will engage in a priorities card sorting activity to identify participant’s 3 main values, which will guide future motivational enhancement and begin to elicit the participant’s view of their first target behavior. After identifying whether they will first tackle sexual health or substance use, the interventionist will assess the participant’s readiness for change, discuss a plan for moving forward, and consider goals. At the end of the session, the interventionist will offer a closing summary and schedule the next session for the following week.

##### Session 2: Second Target Behavior; Continue Focusing and Evoking

The second session will begin with an opening statement to highlight any change talk [50] or goal that was mentioned in the previous session. This session will center primarily on introducing the second target behavior and collaborating on setting the session agenda with the participant. The interventionist will briefly revisit the previous session’s topic and check for any changes or recent events since they last met. Next, they will ask permission to address the second target behavior, all the while using strategies for eliciting change talk and managing discord. Finally, the interventionist will offer a closing summary at the end of the session, highlighting change talk and any steps taken toward change, and schedule the third session during month 1.

##### Session 3: Change Plan

This session will begin by highlighting and integrating change talk on both target behaviors and any ideas or goals the participant has articulated around these behaviors. This will be done collaboratively to set the agenda for the session together. The interventionist will ask permission to discuss collaborating on a change plan together based on the participant’s progress over the last 2 weeks on both goals. Through evoking the participant’s ideas about change, the interventionist will reinforce their self-efficacy for taking steps toward change and offer suggestions on how to adhere to their plan. The interventionist will elicit feedback on a change plan that reflects the participant’s goals, priorities, and readiness to change while anticipating and planning for barriers that may arise in the future. At the end of the session, the interventionist will offer a closing summary highlighting change talk, briefly reiterating the basic plan, and reminding them that the next session will be focused on moving ahead independently.

##### Session 4: Consolidating Commitment; Relapse Prevention or Termination

The final YMHP session will open with the interventionist summarizing the plan developed previously, collaborating on the session agenda based on the participant’s goal updates, and reiterating that this will be the last YMHP session. The participant will discuss how the plan has gone, and the interventionist will manage discord as appropriate while affirming the participant for any steps moving forward. The interventionist will evoke the participant’s ideas about how to adapt the plan in the future should problems arise and develop a backup plan as appropriate. The session will end with a progress summary of the last 4 sessions and a space to reflect on the process of termination with the participant.

### Automated SMS Text Messages (uTECH+YMHP Participants)

Participants assigned to the uTECH+YMHP intervention will receive approximately 2 SMS text messages per week that provide resources promoting sexual wellness and substance use harm reduction. Participants are assigned to specific subgroups based on their answers to the baseline interview to ensure that SMS text messages are tailored. Participants are compensated US $1 per SMS text message to which they respond, and this amount is disbursed at 4 time points corresponding to their 3-, 6-, 9-, and 12-month assessments.

### Incentives

Incentives vary according to intervention and phone type (Figure 1). Participants assigned to the YMHP-only condition will receive US $350, and participants assigned to the uTECH+YMHP condition will receive US $450, including responses to all uTECH messages. The payments for baseline (US $30), 6-month (US $40), and 12-month (Android: US $50; iOS: US $55) interviews are escalated to promote retention in the study. Participants will be paid for each study activity to encourage engagement.

### Discharge From the Study

Participants will be discharged from the study after they complete their 12-month assessment and offboarding. At their final interview, Android-using participants will receive instructions on how to uninstall the eWellness app from their phone. The study team will also discontinue sending automated SMS text messages to uTECH+YMHP participants.

### Ethical Considerations

The research and ethics presented in this study were reviewed and approved by the South Campus institutional review board of the UCLA (#22-000009). The research has also been granted a Certificate of Confidentiality from the National Institutes of Health (CC-OD-22-3555), which deems identifiable information gathered in the course of research not admissible as evidence in any legal processes. Additional terms were provided to ensure confidentiality for the participants. These terms included protection for all study-related data obtained by all uTECH study staff, which includes employees, students, interventionists, and other professionals staffing the project. All participant data will be deidentified and accessible only to staff who completed training in Health Insurance Portability and Accountability Act guidelines and human participants research ethics.

Technical concerns related to data privacy were considered throughout the app development process, which occurred during phase 1 of this project. In collaboration with the UCLA Information Technology and UCLA Compliance departments, considerations related to data storage and data in transit were considered, including the institution’s legal and ethical duties related to the handling of personally identifiable information. Procedures and protocols were established in collaboration with the UCLA Technology Development Group and the UCLA Departments of Computer Science and Engineering.

To enroll in the study, participants would have to review and consent to a study consent form detailing all activities associated with study participation; potential risks and benefits to participation; incentives; and privacy or confidentiality protections granted by the National Institutes of Health Certificate of Confidentiality, UCLA Office of Human Research Protection Program, and study investigators. Participants will be informed during the consenting process that all payments will be made via e-gift card disbursement with a breakdown of all payments totaling the amount of US $350 or US $450 depending on the study group assignment and phone type.

### Primary Outcomes

The primary outcomes that the study will measure are the acceptability, appropriateness, and feasibility of the implementation for uTECH+YMHP and YMHP-only conditions. These primary outcomes will be assessed through surveys conducted at 3-, 6-, 9-, and 12-month time points. The study will measure how outcomes differ between uTECH+YMHP and YMHP-only conditions.

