### This Study

We hypothesize that the uTECH+YMHP intervention will be considered acceptable, appropriate, and feasible by most participants. Furthermore, we hypothesize that participants receiving the combined uTECH+YMHP intervention will show greater and more sustained reductions in substance use and sexual risk behaviors compared to those receiving the YMHP intervention alone. Specifically, we anticipate that the integration of ML-informed SMS text messages will enhance the efficacy of YMHP counseling methods by providing personalized, timely, and contextually relevant support, ultimately leading to improved health outcomes in this sample of SGM young adults.

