## Methods

### Overview

This protocol was created following the SPIRIT (Standard Protocol Items: Recommendations for Interventional Trials) reporting guidelines (Multimedia Appendix 1) [42]. The proposed study is a randomized comparison trial to evaluate the acceptability, appropriateness, and feasibility of uTECH, which is a text-based risk reduction intervention that leverages a data mining and ML algorithm to provide personalized prevention messaging to users. uTECH will be compared to an existing best-evidence MI intervention (YMHP). Participants will be randomly assigned to one of two conditions: (1) uTECH+YMHP (trial intervention+existing intervention) or (2) YMHP only (existing intervention only). Those in the uTECH+YMHP condition will receive 4 YMHP sessions with a trained master’s-level social worker and tailored SMS text messages. Those in the YMHP arm will only receive 4 YMHP sessions. Participants in both conditions will either contribute location-tracking and keylogger smartphone data through an app called “eWellness” (version 1.0.24) or provide data downloads from their most-used, web-based dating and social media accounts. These data will be used to inform and prime the ML algorithm that will be used to make predictions and generate tailored SMS text messages for the uTECH+YMHP condition. The overarching goal of this study is to evaluate the acceptability, appropriateness, and feasibility of uTECH in conjunction with YMHP (condition 1) compared to YMHP alone (condition 2). This study was registered with ClinicalTrials.gov under NCT04710901.

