**Primary**					
	Acceptability, appropriateness, and feasibility of uTECH SMS text messages	Adapted from AIM^a^, IAM^b^, and FIM^c^ [65]		5-item Likert scale	
	Acceptability, appropriateness, and feasibility of Young Men’s Health Project	Adapted from AIM, IAM, and FIM [65]		5-item Likert scale	

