### Sample Size Calculation and Power Analysis

For the power calculation, we used 1 primary outcome, acceptability. We used a balanced repeated measures design [84] with pretreatment baseline measurements. Using a logistic regression generalized linear mixed model [85], we allowed an individual’s 5 measurements (baseline and 3-, 6-, 9-, and 12-month) for acceptability to be correlated via an autoregressive-1 structure. With an initial sample size of 330 (to account for 95% retention), an autocorrelation of 0.1, and a baseline effectiveness of 85%, we aimed to detect a minimum time-averaged difference of 9% in acceptability between any 2 conditions, maintaining 80% power and an a priori α level of .05. This calculation was based on pairwise comparisons between uTECH+YMHP versus YMHP-only conditions. If the autocorrelation [86] between measures within the same individual was as high as 0.5, the sample size was adjusted to detect a minimum difference of 11% between the 2 conditions. A 9% to 11% difference between the 2 conditions is considered statistically significant, given the existing evidence supporting YMHP and the relative cost-effectiveness and ease of delivery of the uTECH intervention. The ability to demonstrate a small increase in the acceptability of uTECH over YMHP will support the widespread implementation of uTECH in future efficacy trials.

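### The only listed primary scale that both arms can answer rates YMHP, so the randomised contrast cannot show that uTECH is acceptable, or more acceptable than YMHP

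*Protocol article*

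**What the plan says.** All references are to the protocol article.

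- **Primary Outcomes** attaches the outcomes to the two arms, as the "acceptability, appropriateness, and feasibility of the implementation for uTECH+YMHP and YMHP-only conditions", measured at 3, 6, 9 and 12 months. It adds: "The study will measure how outcomes differ between uTECH+YMHP and YMHP-only conditions". Planned Analytic Approach also words the outcomes per intervention condition and analyses treatment effects with growth curves.
- **Table 2** lists two primary outcomes, both measured with items adapted from AIM, IAM and FIM: "Acceptability, appropriateness, and feasibility of uTECH SMS text messages" and "Acceptability, appropriateness, and feasibility of Young Men’s Health Project".
- **Overview** fixes who receives what: "Those in the uTECH+YMHP condition will receive 4 YMHP sessions with a trained master’s-level social worker and tailored SMS text messages". For the comparator: "Those in the YMHP arm will only receive 4 YMHP sessions".
- **This Study** states the first hypothesis: "We hypothesize that the uTECH+YMHP intervention will be considered acceptable, appropriate, and feasible by most participants".
- **Sample Size Calculation and Power Analysis** powers the trial on acceptability without saying which scale. It ends by stating that "a small increase in the acceptability of uTECH over YMHP will support the widespread implementation of uTECH" in future efficacy trials.

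**The concern.** A randomised comparison needs the same question put to both arms. The text messages exist in one arm only, so the scale that rates them has no comparator. The scale that does have a comparator rates the counselling that both arms receive. The conclusion in the power section is about uTECH, and neither listed scale compared between arms estimates that quantity.

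The primary result could therefore be read wrongly in either direction. The YMHP contrast could be null while participants like the texts, or positive while they dislike them. The problem also carries forward. Planned Analytic Approach reads an intercept difference as a post-intervention effect, and Mediation and Moderation makes its post hoc work conditional on significant treatment coefficients for these same outcomes. Both presuppose an outcome that means the same thing in each arm.

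**Working it through.** **1. Who can answer which scale.** Inputs: 165 per arm (Target Population) and 95% retention (power section). 165 × 0.95 = 156.75, about 157.

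| Scale in Table 2 | uTECH+YMHP | YMHP only | What a between-arm difference means |
|---|---|---|---|
| uTECH texts | about 157 | 0 | not defined |
| YMHP | about 157 | about 157 | effect of adding texts on how YMHP is rated |
| Whole assigned condition | none listed | none listed | would match the Primary Outcomes wording |

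**2. Does the YMHP contrast carry information about the texts?** Suppose 85% rate YMHP acceptable in both arms. The expected contrast is 0.85 − 0.85 = 0. It stays 0 whether 20%, 50%, 85% or 95% of the uTECH+YMHP arm find the texts acceptable, because text acceptability does not enter it.

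**3. Does the powered endpoint match a listed scale?** The power section models five acceptability measurements including baseline. Primary Outcomes lists four, starting at 3 months, and neither intervention can be rated from experience before it is received. The powered variable is therefore not visibly either Table 2 scale.

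For completeness, I tried to reproduce the stated N of 330 (85% baseline, 9 points, autocorrelation 0.1, 80% power, α .05 taken as two-sided).
- Single-time-point n per arm = [1.96√(2p̄(1−p̄)) + 0.8416√(p₁(1−p₁) + p₂(1−p₂))]² / d². This gives 181 for 85% vs 94% and 304 for 85% vs 76%.
- AR(1) factor for the mean of five measurements = [5 + 2(4×0.1 + 3×0.01 + 2×0.001 + 0.0001)] / 25 = 0.2346.
- 181 × 0.2346 = 42.5, so 43 per arm, and 86 / 0.95 gives 91 in total. 304 × 0.2346 = 71.3, so 72 per arm, and 144 / 0.95 gives 152.

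The stated 330 is not reproduced. On this formula it is more than enough (power 98.6% to 99.97%). The mismatch does not bear on the present point, since a larger N would not turn a rating of YMHP into a rating of uTECH.

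**4. What the text scale can deliver.** The half-width of a 95% CI for one proportion at one time point is 1.96√(p(1−p)/n). With p = 0.85 (an assumption: the article gives 85% as a baseline figure for its power model, not for the texts) and n = 157, this is 1.96 × √(0.1275/157) = 0.056, or ±5.6 points. The Results section reports 301 of 424 completing 12 months. If about half of these, 150, were in the uTECH+YMHP arm (the split is not given), the half-width is 1.96 × √(0.1275/150) = 0.057, or ±5.7 points.

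**The case against.** The best defence has four parts.

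*There is a common outcome.* Everyone receives YMHP, so the YMHP scale supports a valid randomised contrast. This stands. A reader might infer that the arms share no primary outcome at all, and the documents do not support that. The difficulty is what the shared outcome measures.

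*The plan never says it will set text ratings in one arm against YMHP ratings in the other.* This also stands. The power section's closing phrase tempts one to infer such a comparison, in which the object rated would be completely confounded with arm. But the same section describes its comparison as one between conditions, and the Overview uses similar shorthand just before it defines the two arms. The phrase may be loose wording, and no section names that cross-object analysis. Even read as shorthand for the two conditions, however, it needs a condition-level rating that Table 2 does not list.

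*Item wording and scoring belong in the full protocol or analysis plan.* This is fair as to detail, and a condition-level score may have been intended. But Table 2 does name the objects rated. A package score built from both sets in one arm and from the YMHP set alone in the other would still not use identical items.

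*The first hypothesis can be answered descriptively.* True for the texts. It is a one-arm statement that the text scale can address, and a benchmark for 'most' may sit in the analysis plan. What remains is that the between-arm model does not answer it.

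**Conclusion.** The point holds as a mismatch between the listed primary instruments, the promised contrast and the conclusion attached to it. With the Table 2 scales, the randomised contrast estimates the effect of adding texts on ratings of YMHP. It does not estimate whether uTECH is acceptable, or more acceptable than YMHP, and the powered acceptability endpoint is not tied to either scale.

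The size is structural: about 157 against 0 respondents on the text scale. No bias in points can be derived, because the documents give no figure for how ratings of texts and of counselling differ. The one-arm estimate for the texts is reasonably precise, at about ±5.6 points under the assumed 85% and 95% retention.

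The conclusion rests on Table 2 being the complete list of primary instruments. If a condition-level rating with identical items was collected in both arms, naming it would resolve the point.

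**What to change.** Reconcile Primary Outcomes, Table 2, Planned Analytic Approach and the power section.

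**If a condition-level rating with identical items was collected in both arms,** name it as the randomised and powered endpoint.

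**If not:**
1. Define the randomised contrast as the YMHP AIM/IAM/FIM scores in both arms, interpreted only as the effect of adding uTECH on how YMHP is rated.
2. Report acceptability, appropriateness and feasibility of the uTECH texts as one-arm estimates with 95% CIs, against a benchmark for 'most' that the sponsor states. The article gives none.
3. Delete the closing claim of the power section or reword it to rest on item 2. Label any within-person comparison of text and YMHP ratings in the uTECH+YMHP arm as non-randomised. Such a comparison removes confounding with arm but still sets two different objects side by side.

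**Cost.** Only analysis wording changes, since data collection has ended. The headline uTECH result becomes a one-arm estimate in place of a randomised comparison. The Results section says analysis is under way, so the change should be dated and disclosed as made after data collection.
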